### Eligibility

Female individuals of 13–18 years of age who are currently patients at the eating disorder clinic and newly diagnosed with AN according to the Diagnostic and Statistical Manual of Mental Disorders, 5th edition^(58)^, and treatment naïve will be eligible. Healthy control participants will be matched on age, sex and education level with the AN participants. The clinical diagnosis/diagnoses for participants will be validated/ruled out by the Schedule for Affective Disorders and Schizophrenia for School-Age Children – Present and Lifetime version^(59)^. The presence of other exclusion criteria will also be further explored at the clinical visit.The exclusion criteria are as follows:Having one or several chronic medical conditions that may interfere with or hinder participation or affect study outcomes.Use of medications that affect hormone levels or eating behaviours.Having one or several severe psychiatric disorders other than AN (e.g. schizophrenia, major depressive disorder, bipolar disorder).Current drug abuse, pregnancy or potential pregnancy (for AN patients, these conditions are excluded as a part of routine care. For healthy controls, no drug testing will be performed.).High risk of refeeding syndrome or severe complications related to eating disorders.Inability to comply with the nutritional programme of the study.Allergies to foods included in the provided meal content.Cognitive impairments preventing comprehension of the study or the informed consent process.Contraindications for MRI (e.g. pacemaker, prosthesis, claustrophobia)Fasting blood sugar above 6·0 mmol/l on the morning of the study, as this indicates either non-compliance with overnight fasting or pre-diabetes/diabetes.

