### Assessments for description of sample

Body weight and height will be measured at T_-1_ to calculate BMI. At the same time, the participants’ sociodemographic background will be assessed using a brief self-made questionnaire. Additionally, at T_-1_, the following self-rating scales will be collected for screening purposes and description of sample: (1) the Autism Spectrum Screening Questionnaire^(60,61)^, (2) the Childhood Trauma Questionnaire^(62)^, (3) Children’s Depression Inventory^(63)^, (4) the Screen for Child Anxiety Related Disorders^(64)^, (5) the Eating Attitudes Test^(65)^ and (6) the Global Assessment of Functioning scale^(66)^.

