#### Descriptive statistics

Baseline data and descriptive statistics will be reported using standard measures in accordance with Consolidated Standards of Reporting Trials guidelines, and the baseline characteristics of the included participants will be reported per randomisation group and AN status in a baseline table. The following baseline characteristics will be reported: age (years), AN subtype (by categories), co-morbidity (% yes, by diagnostic categories), smoking (% yes, frequency), country of birth (% Turkey, % first-generation immigrant and % second-generation immigrant – with at least one parent born outside of Turkey). Sex will not be reported as all participants will be of female sex.

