#### Primary analysis

For the statistical analysis of functional neuroimaging data, MATLAB and Statistical Parametric Mapping (SPM12) software will be used to assess brain activity patterns and differences across groups. Connectivity analysis will be performed using the CONN Toolbox to examine the relationships between different brain regions and networks. Neuroimaging data will first undergo pre-processing to ensure the data is suitable for further statistical analysis.

The pre-processing steps that will be performed include the following:Realignment: This is the process of correcting head motion of the participants.Slice-Time Correction: This involves correcting for functional differences between slices acquired every 3 s.Coregistration: Anatomical and functional images are overlaid to determine the anatomical location of activation.Spatial Normalisation: This process accounts for individual brain shapes by normalising anatomical MRI images. The template developed by the Montreal Neurological Institute will be used.Smoothing: This is used to improve image quality and will be performed using a 3D Gaussian kernel (full width at half maximum = 8 mm).

After the pre-processing steps, the data of all participants will be registered to the common Harvard–Oxford Cortical Atlas space. Participant and group-level regression analyses will be performed in this atlas space. Functional connectivity analyses will be performed between regions of the components of the Salience Network, including the anterior insula, dorsal anterior cingulate cortex, temporoparietal junction and hypothalamus. Changes in the topology of networks formed by these four regions, in addition to their functional connectivity with each other, will be analysed using Graph Theory. The changes in the connectivity features of these regions before and after caloric/non-caloric intake will be evaluated using both nodal and global metrics. Significant results obtained will be recalculated using masks transferred back to the participant space. Beta values of the regression analysis will be controlled for type-1 errors with false discovery rate and reported accordingly.

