The independent variables of the regression analyses will include (1) type of meal (caloric or non-caloric), (2) AN status (AN or healthy control), (3) AN subtype (restrictive or bulimic type), (4) BMI and (5) duration of AN illness. A random effect for each participant and for each matched set of patient and healthy control will be used to account for within-subject correlations from repeated measurements and dependencies within each matched pair.

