#### Secondary analyses

Secondary outcome variables will be modelled using similar regression models as used in the primary analysis. In these models, time (T_0_/T_1_/T_2_) and the allocation by time interaction will be included as fixed effects, and a random intercept for each subject will be included when analysing variables that are measured at more than two timepoints. Additional parametric tests will be performed as long as the assumptions for them are met. Depending on the type of data, the following statistical methods will be used: Independent *t* test, Pearson *r* and ANOVA. Where necessary, corresponding non-parametric alternatives will be used.

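### BMI enters the regression unstandardised and without an age term in girls aged 13–18, so the BMI and BMI-adjusted AN-status coefficients partly carry age

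*Protocol article*

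**What the plan says.** All references are to the protocol article.

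- **Regressors.** Under Statistical methods, Primary analysis, the independent variables are meal type, AN status and "3) AN subtype (restrictive or bulimic type), (4) BMI and (5) duration of AN illness". Age is not listed.
- **Derivation of BMI.** Assessments for description of sample states: "Body weight and height will be measured at T_-1_ to calculate BMI". No z-score, percentile or percent of median appears anywhere.
- **Population.** Eligibility covers "Female individuals of 13–18 years of age who are currently patients at the eating disorder clinic".
- **Age by design.** Eligibility also states: "Healthy control participants will be matched on age, sex and education level with the AN participants".
- **Matching in the model.** Primary analysis adds: "A random effect for each participant and for each matched set of patient and healthy control will be used". The pair effect is random, not fixed.
- **Age in the analysis.** It appears only under Descriptive statistics: "The following baseline characteristics will be reported: age (years), AN subtype (by categories".
- **Where the model is reused.** Secondary analyses states: "Secondary outcome variables will be modelled using similar regression models as used in the primary analysis". Dose–response analyses adds the amount of meal-1 eaten to the same models.

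**The concern.** The evident purpose of BMI in this model is to represent degree of underweight. In adolescents it does so only relative to age, because the same BMI means something different at 13 and at 18.

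Age matching balances age between patients and controls before BMI is adjusted for. It does not protect the BMI slope. With a random pair effect, that slope is a weighted mean of a within-pair part, where age cancels, and a between-pair part, where older pairs have both higher BMI and a different outcome level if the outcome varies with age. Patients have much lower BMI than controls, so an error in the slope is multiplied by the group gap and moves into the AN-status coefficient.

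At stake is the reading of the adjusted patient–control difference and of the BMI effect, for any outcome analysed as a level. The hormones, blood pressure, pulse, self-ratings and meal-2 intake modelled under Secondary analyses are the natural candidates.

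**Working it through.** **Plan's own figure.** The plan gives no number on this point. The only related one is the sample size: 34 per group for d = 0.6, 70% power, two-sided 0.05. The normal approximation gives 2(1.960 + 0.524)²/0.6² = 34.3, so 35. The exact t calculation gives 36 (power 68.4% at 34, 70.9% at 36). Nothing below depends on this; d = 0.6 is used only for scale.

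**Share of BMI variance due to age (inputs assumed).** Ages are even over 13–18, median BMI rises 0.4–0.6 kg/m² per year, and patients are at 80% of median with a BMI SD of 1.5.

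- Age SD = 5/√12 = 1.443 years.
- Age-driven BMI SD = 0.8 × 0.4 × 1.443 = 0.46, or 0.8 × 0.6 × 1.443 = 0.69 kg/m².
- Share = 0.46²/1.5² ≈ 9% to 0.69²/1.5² ≈ 21%. With an SD of 2.0 it is 5% to 12%.

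**Simulation A.** 36 exactly age-matched pairs; median BMI 18.5 at age 13; patients' percent of median N(80, 7) clipped to 60–95, controls' N(100, 10); pair SD 0.3, residual SD 1; REML with a pair intercept; covariates AN status, meal and BMI; true BMI and AN effects zero; 6,000 runs per cell.

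| BMI slope (kg/m² per year) | Age effect (SD per year) | BMI coefficient | False positives, BMI | AN-status bias (SD) |
|---|---|---|---|---|
| 0.4 | 0.1 | 0.021 | 6.8% | 0.08 |
| 0.4 | 0.3 | 0.058 | 12.8% | 0.22 |
| 0.6 | 0.1 | 0.030 | 7.7% | 0.12 |
| 0.6 | 0.3 | 0.078 | 20.2% | 0.31 |

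- With percent of median BMI in the same cells, the coefficient is within 0.001 of zero, false positives are 5.2–5.8%, and AN-status bias is within 0.01.
- With no age effect on the outcome, BMI as listed gives a coefficient of 0.00 and 5.5–6.0% false positives.
- The meal coefficient is within 0.01 of zero throughout.
- In repeat runs, AN-status false positives were 10–14% at 0.3 SD per year. At 0.1 they were 7–8.5%, against about 6% with no age effect.

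**Simulation B, different inputs.** Ages uniform 13–19; BMI SD 1.2 in patients and 2.5 in controls; gap 5 kg/m²; BMI slopes 0.3–0.7; age effects 0.1–0.3; 500 runs per cell.

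- The spurious BMI coefficient is 0.02–0.10 and the spurious AN-status coefficient 0.11–0.52 SD.
- Rejection is 7–40% for BMI and 8–28% for AN status. With no age effect it was 6% and 8%, so the lowest cells cannot be told from the null.
- In the central case (0.5, 0.2) the coefficients are 0.057 and 0.30 SD. With controls matched only to within an SD of 0.5 year they are 0.054 and 0.26.
- Adding age gives 0.003 and 0.009. Age-standardised BMI gives about zero for both.

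**Hand check of the central case.** Split each pair into scaled sum and difference, with weights w_B = 1/(1+ρ) and w_W = 1/(1−ρ). The fitted within-pair correlation ρ was 0.169.

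- Var(age) = 6²/12 = 3.
- Between-pair BMI variance: V_B = 2 × 0.5² × 3 + (1.2² + 2.5²)/2 = 1.5 + 3.845 = 5.345.
- Within-pair BMI variance: V_W = 3.845.
- Between-pair covariance with the outcome: C_B = 2 × 0.5 × 0.2 × 3 = 0.6. Within pairs it is 0.
- BMI coefficient ≈ w_B·C_B/(w_B·V_B + w_W·V_W) = 0.855 × 0.6/(0.855 × 5.345 + 1.203 × 3.845) = 0.513/9.20 = 0.056 (simulated 0.057).
- AN-status bias ≈ 0.056 × 5 = 0.28 SD (simulated 0.30).

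**The case against.** The strongest reply is that this misses the main question. The primary objective concerns the response to caloric and non-caloric meals and how it differs by group, and Primary analysis says: "The changes in the connectivity features of these regions before and after caloric/non-caloric intake will be evaluated". The randomised meal contrast is unbiased, and an age effect that is equal before and after the meal drops out of a change. No stated hypothesis concerns a BMI coefficient. All of this stands, and it is why the point is minor.

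The size is also wholly assumed. At 0.3 SD per year the outcome shifts 1.5 SD between 13 and 18, which is strong. At 0.1 the AN-status bias of 0.08–0.12 SD is small against a standard error of about 0.36. The simulations use one observation per person and omit the participant effect, AN subtype and illness duration. These limits also stand: the figures show direction and plausible range, not a prediction.

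It can be said that the form of a covariate belongs in an SAP, and that the regressor list is worded as inclusive rather than closed. This carries less weight. The article names the covariate and how it is obtained and offers no age term, so a literal reading gives the model examined here.

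Finally, an age term works as well as standardisation. That is correct. It widens the choice of remedy but does not remove the defect.

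**Conclusion.** The concern holds, at low severity. As written, the BMI coefficient and the BMI-adjusted AN-status coefficient partly carry age wherever the outcome level varies with age. Under the assumptions of simulation A, the AN-status shift runs from 0.08 SD, about an eighth of the design effect of 0.6, to 0.31 SD, about half of it. The wider inputs of simulation B reach 0.52 SD.

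There is no bias if the outcome does not vary with age. Before–after change is affected only if age alters the response to the meal.

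**What to change.** In Assessments for description of sample and in Primary analysis, replace BMI with percent of median BMI or a BMI-for-age z-score, and name the one reference population used. Carry the same variable into the models under Secondary analyses and Dose–response analyses, and report unstandardised BMI only descriptively. Keeping BMI and adding age as a covariate would also remove the bias; the standardised form has the further merit that its coefficient reads directly as degree of underweight.

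The cost is one derived variable, a few words in two sections, and a documented protocol change. Age, height and weight are already recorded, so no visit or measurement is added. Analysis starts only after data collection is complete, with no interim look, so the change can be made before any results are seen.

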#### Secondary analyses

Secondary outcome variables will be modelled using similar regression models as used in the primary analysis. In these models, time (T_0_/T_1_/T_2_) and the allocation by time interaction will be included as fixed effects, and a random intercept for each subject will be included when analysing variables that are measured at more than two timepoints. Additional parametric tests will be performed as long as the assumptions for them are met. Depending on the type of data, the following statistical methods will be used: Independent *t* test, Pearson *r* and ANOVA. Where necessary, corresponding non-parametric alternatives will be used.

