### Outcome measures

Outcome measures will be assessed at baseline before randomisation (T_0_), 15 min after meal-1 (T_1_), 1 h after meal-1 (T_2_) and 3 h after meal-1 (T_3_), with some measures collected only at specific timepoints. Details for each outcome measure are provided under their respective subheadings and summarised in Table 2. If a participant misses a scheduled data collection timepoint, the following steps will be taken in sequence: (1) if feasible and meaningful, the data will be collected as soon as the issue is identified; (2) if not, the data point may be recorded as missing, and the participant will continue in the study; or (3) if the participant is deemed no longer relevant to the study, they will be excluded from further follow-up and per-protocol analysis.

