#### Sample size calculation

A two-tailed power calculation for 70 % power and *P* = 0·05 was performed using G * Power software, for a *t* test with linear regression (two independent groups) and an effect size of d = 0·6, based on results from similar neuroimaging studies^(42)^, determining that thirty-four participants per group (AN/healthy) would be sufficient. To account for potential dropouts or unforeseen issues, thirty-six participants will be recruited for each group to ensure robust statistical analysis.

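### The secondary models treat the pre-meal T0 value as a response, so the meal effect is a change-from-T0 contrast: valid, but less precise than adjusting for T0

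*Protocol article*

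**What the plan says.** The Secondary analyses section of the protocol article builds on the primary model: "Secondary outcome variables will be modelled using similar regression models as used in the primary analysis". It then gives T0 its role, as one of the three levels of time (T0, T1 and T2), and states that "the allocation by time interaction will be included as fixed effects, and a random intercept for each subject will be included", the intercept being for variables with more than two timepoints.

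The terms carried over are listed under Primary analysis: "The independent variables of the regression analyses will include (1) type of meal (caloric or non-caloric", followed by AN status, AN subtype, BMI and illness duration. The T0 value of the outcome is not on that list, and neither section constrains the T0 means.

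On timing, the Outcome measures section states: "Outcome measures will be assessed at baseline before randomisation". The visual analogue scales are collected at T0, T1, T2 and T3. Hormones, blood pressure and pulse are collected at T0 and T2 only. Meal-2 intake has no T0 value and is not affected by this point.

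**The concern.** T0 precedes meal-1, and the meal is randomised and masked, so no true meal difference is expected at T0 among those randomised. A model with meal, time and meal-by-time nevertheless estimates one. The meal effect at T1 or T2 is then measured against that noisy estimate and carries the full sampling error of T0.

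Precision is what is at stake. The trial's hypotheses include that calories worsen fear of gaining weight and the feeling of being overweight in patients. Both are scales with a T0 value, and with 1:1 allocation of 36 patients the patient contrast is about 18 against 18. A comparison of that size has little precision to spare.

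**Working it through.** **Inputs from the protocol article.** Two-sided 0.05 (Analysis plan). Target power 70%, 34 per group calculated and 36 recruited, and "an effect size of d = 0·6, based on results from similar neuroimaging studies" (Sample size calculation). Patients are allocated 1:1 and each control takes the matched patient's allocation (Randomisation), which gives about 18 per meal in patients and 36 per meal overall.

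**Assumptions.** The outcome SD is 1 at each timepoint. The d = 0.6 was set for the AN/healthy imaging comparison and is borrowed here for the meal contrast. The correlation rho is not stated, so it is varied. Correlation within matched pairs is ignored.

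**The plan's own figure.** n = 2(1.960 + 0.524)²/0.6² = 34.3 per group, or 35 rounded up. At 34 per group, power is 69.6% by the normal formula and 68.4% by the non-central t. The stated 34 is reproduced to within one participant.

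**What the coefficient estimates.** Write the non-caloric means as m at T0 and m + t at T2, and the caloric means as m + b at T0 and m + b + t + g at T2. Here b is the meal main effect and g the interaction. Then g = (caloric T2 − caloric T0) − (non-caloric T2 − non-caloric T0), the difference in change.

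**Variance per participant.**
- Change from T0: 2(1 − rho)
- Adjusted for T0: 1 − rho²
- Ratio: 2(1 − rho)/[(1 − rho)(1 + rho)] = 2/(1 + rho), which exceeds 1 for every rho below 1.

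At rho = 0.5 with 36 per meal, the change contrast has SE √(2/36 × 1) = 0.2357 and the adjusted contrast has SE √(2/36 × 0.75) = 0.2041. The variance ratio is 1.333. Generalised least squares with a random-intercept covariance gives these same two standard errors with two or three timepoints, with the T0 meal effect left free and then constrained to zero.

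**Power.** Non-central t with non-centrality (0.6/s)√(n/2), where s is the square root of the variance above. Degrees of freedom are 2n − 2 for change and 2n − 3 for adjusted. Gains come from unrounded values.

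| Per meal | rho | Change from T0 | Adjusted for T0 | Gain (points) |
|---|---|---|---|---|
| 36 | 0.3 | 56.4% | 74.9% | 18.5 |
| 36 | 0.5 | 70.9% | 82.6% | 11.7 |
| 36 | 0.7 | 90.0% | 94.0% | 4.0 |
| 36 | 0.8 | 97.8% | 98.7% | 0.9 |
| 18 | 0.3 | 31.5% | 44.9% | 13.4 |
| 18 | 0.5 | 41.7% | 52.3% | 10.6 |
| 18 | 0.7 | 61.7% | 68.7% | 7.0 |
| 18 | 0.8 | 79.0% | 82.9% | 4.0 |

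For reference, the T2 value alone, ignoring T0, gives 70.9% with 36 per meal and 41.7% with 18. The change contrast equals this at rho = 0.5, falls below it at lower rho and exceeds it at higher rho.

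**The case against.** The strongest reply is that nothing here is an error. Allocation-by-time with a subject random intercept is a standard analysis of randomised repeated measures, unbiased and with correct type 1 error. This stands. A reader might infer that chance T0 imbalance in cells of 18 biases the planned estimate. It can pull a single realised estimate through regression to the mean, but under randomisation it does not bias the estimator.

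A reader might also infer that the baseline is thrown away, or that a fixed 11 points of power is lost. The protocol supports neither. The change contrast is no better than ignoring T0 only at rho of 0.5 or below. The loss depends on a correlation the protocol does not give and on an effect size set for another comparison.

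A further objection is that randomisation makes T0 means equal in expectation only in the set as randomised. The Adherence section restricts the primary analysis to adherent participants, and its criteria include how much of meal-1 was eaten. No other set is named for the secondary models. Suppose, for illustration, that such selection left a T0 difference of 0.2 SD that persisted to T2. Adjusting at rho = 0.5 would leave a bias of 0.2 × (1 − 0.5) = 0.1 SD, and the change contrast would leave none. Other selection patterns could favour adjustment. This stands as a small cost of the change.

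Finally, the free meal effect is read from two sections together, and an article may leave parameterisation to a fuller plan. But the text does assign T0 a role, as a level of the time factor, and the reading follows from the terms it lists.

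One possible counter does not help the plan. The Randomisation section has the envelope drawn the evening before, so allocation may precede T0. T0 is still taken before the meal and under masking, so the argument for equal T0 means holds among all those randomised.

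**Conclusion.** The point holds as an improvement in efficiency, not as a flaw in validity. For secondary outcomes with a T0 value, the planned meal effect is a difference in change, with variance 2/(1 + rho) times that of the T0-adjusted effect. On the assumptions above, the power forgone runs from 18.5 points (rho 0.3) to 0.9 (rho 0.8) with 36 per meal, and from 13.4 to 4.0 with 18 per meal. It is worth having if rho is moderate or low and is minor at 0.8 or above. It does not rescue the patient-only comparison, which at rho = 0.5 stays near 50% power either way. The protocol claims no power for secondary outcomes, so no stated figure is overturned.

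**What to change.** For each secondary outcome with a T0 value, state that the meal effect is estimated on the post-meal values with T0 as a covariate.

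- Scales with several post-meal times: keep the subject and pair random effects.
- Hormones, blood pressure and pulse: use one T2 row per participant, with T0 as covariate and the pair random effect only. With a single row per participant, a subject intercept cannot be separated from the residual.

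Alternatively, keep T0 in the mixed model but constrain its mean to be equal for the two meals within each AN status, fitted to all randomised participants with data.

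Where a per-protocol subset is analysed, report the change-from-T0 contrast as a sensitivity analysis.

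The cost is a few lines in the analysis plan, recorded as a change. No new data or change in conduct is needed, and because analysis starts only after data collection ends, it can be fixed beforehand.

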While these observations indicate that neuronal networks in the brain integrate metabolic and psychological aspects of eating differently in AN, it is unclear how this perturbed metabo–psychological integration contributes to AN development and maintenance^(52)^. No previous report has, to our knowledge, revealed in what way the connection between psychology and metabolism mediates core symptoms of AN; that is, no one has distinguished either what neuronal networks respond to the psychological *contra* metabolic aspects of eating a meal or how those networks integrate their information to affect patients’ food intake, distorted body image and fear of weight gain. The identification of the mechanisms that drive AN is also hampered by the current tendency of published studies to focus on adults rather than adolescents although adolescence is the time when most patients develop AN. The ISRCTN and Clinicaltrials.gov registers (as of October 2025) record neither any recent nor ongoing trials anywhere in the world aimed to answer these questions. No current clinical trials of AN comprehensively speak to metabo–psychological mechanisms of change.

The primary objective of the Networks Integrating Anxiety and Metabolism in Anorexia Nervosa (NAMA) trial is to distinguish between the neural response to eating caloric and non-caloric meals and how this differs between newly diagnosed adolescents with AN and matched healthy controls. Secondary objectives examine the effects of caloric and non-caloric food intake on endocrine, circulatory, psychological and behavioural responses in patients with AN and healthy controls. By integrating behavioural, psychological and physiological aspects of food intake with brain network analyses, the NAMA trial will investigate what drives AN. We hypothesise that calorie-dependent changes in network activity will differ between AN patients and healthy controls and that calorie intake will predict aggravated AN-related symptoms in patients: lower food intake, worse fear of gaining weight and increased feeling of being overweight.

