#### Secondary outcome measures

##### Self-report

At T_0_, T_1_, T_2_ and T_3_, psychometric evaluations will be performed on Visual Analogue Scales. The following questions will be used at the appropriate timepoints:How anxious are you about consuming the meal? Response options: I feel no anxiety – I feel very anxious.How often do you feel anxious about eating unfamiliar foods? Response options: I do not feel anxious – I feel very anxious.How hungry do you feel? Response options: I feel full – I feel very hungry.How worried are you about the possibility of gaining weight from consuming the meal? Response options: I feel no anxiety – I feel very anxious.How much do you fear becoming obese? Response options: I do not fear – I fear a lot.How much does the thought of becoming obese affect your eating habits? Response options: It does not affect at all – It affects a lot.How overweight do you feel? Response options: I feel very thin – I feel very overweight.

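### The random intercept for the repeated symptom ratings assumes equal variance and correlation at T0, T1 and T2, so the standard errors of single meal-by-time contrasts can be wrong in either direction

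*Protocol article*

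**What the plan says.** Protocol article, Secondary analyses: "Secondary outcome variables will be modelled using similar regression models as used in the primary analysis". The fixed part of the model is then extended by time, over T0, T1 and T2, and by its interaction with allocation. The random part is described as follows: "a random intercept for each subject will be included when analysing variables that are measured at more than two timepoints".

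Primary analysis, the model carried over: "A random effect for each participant and for each matched set of patient and healthy control will be used". The article gives the participant effect the job of handling correlation between repeated measurements, and the matched-set effect the job of handling dependence within pairs.

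Self-report: "At T_0_, T_1_, T_2_ and T_3_, psychometric evaluations will be performed on Visual Analogue Scales". Blood markers, blood pressure and pulse are taken at T0 and T2 only, so the clause on more than two timepoints concerns the symptom ratings.

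The hypotheses, stated just before Experimental methods, predict that calories will lead in patients to "lower food intake, worse fear of gaining weight and increased feeling of being overweight". The last two of these three are symptom ratings.

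**The concern.** A subject random intercept with independent residuals makes the ratings equally variable at each timepoint and equally correlated for each pair. The schedule gives reason to doubt that. T0 is rated fasted, before meal-1. T1 and T2 are rated 15 minutes and one hour after the same meal, so they may agree with each other better than either agrees with T0. Ratings may also be most variable soon after the meal: the section on adverse events expects anxiety at being asked to eat and symptom fluctuation around meals.

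The model uses a single pooled residual variance for every time contrast. If the true variances of the pairwise differences are unequal, that pooled figure is too small for some contrasts and too large for others. The 95% intervals and the 0.05 level promised in the Analysis plan are then not delivered for individual allocation-by-time coefficients, and some of those coefficients may be used to test the fear and feeling-overweight predictions.

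**Working it through.** **The plan's own figure.** The article states no correlation, no SD by timepoint and no standard error for any rating, so there is nothing on this point to reproduce. Its one calculation, 34 per group, reproduces approximately: 2 × ((1.960 + 0.524)/0.6)² = 34.3. It does not bear on this point.

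**Inputs.** There are 36 patients randomised 1:1, and each control takes the matched patient's allocation, so about n = 36 per meal arm. Timepoints are T0, T1 and T2; alpha is 0.05 two-sided. All correlations and SDs below are assumptions. Data are taken as complete and balanced.

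**Formulae.** Let S be the true within-subject covariance over k = 3 timepoints.

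- Residual variance that the random-intercept model estimates: s² = (trace S − sum S / k)/(k − 1).
- Variance that the model gives to any allocation-by-time contrast: (4/n) s².
- True variance of the T2−T0 contrast: (2/n) Var(Y_T2 − Y_T0).
- Ratio of model SE to true SE: √(2s² / Var(Y_T2 − Y_T0)). T1−T0 is treated the same way. The ratio does not depend on n.
- Approximate type I error: 2[1 − Φ(1.977 × ratio)], where 1.977 is the t quantile on 2 × (72 − 2) = 140 degrees of freedom.

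**Example A, correlations 0.6/0.6/0.8** (T0–T1 / T0–T2 / T1–T2), unit SDs. sum S = 3 + 2 × 2.0 = 7, so s² = (3 − 7/3)/2 = 0.333. Var(T2−T0) = 2 − 1.2 = 0.8. Ratio = √(0.667/0.8) = 0.91.

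**Example B, 0.4/0.7/0.4.** sum S = 3 + 2 × 1.5 = 6, so s² = 0.5. Var(T2−T0) = 0.6, ratio √(1/0.6) = 1.29. Var(T1−T0) = 1.2, ratio √(1/1.2) = 0.91.

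**Results.** Rejection rates with no true effect come from simulation (40,000 trials per setting). Those marked ≈ use the approximation above.

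| Assumed pattern | T2−T0: SE ratio | T2−T0: type I | T1−T0: SE ratio | T1−T0: type I |
|---|---|---|---|---|
| 0.6/0.6/0.6 | 1.00 | 5.0% | 1.00 | 5.0% |
| 0.6/0.6/0.8 | 0.91 | 7.4% | 0.91 | 7.4% |
| 0.6/0.5/0.8 | 0.86 | 9.3% | 0.96 | ≈5.8% |
| 0.5/0.4/0.8 | 0.85 | 9.4–9.6% | 0.93 | ≈6.6% |
| 0.4/0.3/0.7 | 0.87 | 8.6–8.8% | 0.94 | ≈6.2% |
| 0.5/0.7/0.5 | 1.20 | 1.9% | 0.93 | 6.9% |
| 0.4/0.7/0.4 | 1.29 | 1.1% | 0.91 | 7.1% |
| 0.6 throughout, T1 SD × 1.5 | 1.24 | 1.6% | 0.92 | 7.0% |
| 0.6 throughout, T1 SD × 1.3 | 1.13 | 2.7–2.9% | 0.95 | ≈6.0% |
| 0.6/0.6/0.8, T1 SD × 1.3 | 1.03 | 4.3% | 0.87 | 8.9% |

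Correlation that falls steadily with lag (first-order autoregressive, 0.3 to 0.9) gives T2−T0 ratios of 0.92 to 0.83 and type I error of 6.9% to 10.2%.

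**Why the errors come in pairs.** With balanced data, 2s² is the average of the three pairwise difference variances. In example A these are 0.8, 0.8 and 0.4, with mean 0.667 = 2s². Unless all three are equal, at least one contrast has too small an SE and another too large. Both contrasts against T0 can be conservative only if T1 and T2, 45 minutes apart after one meal, are the least alike pair.

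**Omnibus test.** The two-degree-of-freedom allocation-by-time test rejects at 5.8%, 5.8%, 6.2% and 5.8% in the four equal-variance patterns where T1–T2 is highest.

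**Alternative.** In the equal-correlation pattern and the four patterns with T1–T2 highest, a test based on the contrast's own variance, as an unstructured covariance provides, rejects at 4.8% to 5.2%.

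**The case against.** A reader might infer that the T2−T0 error bars are simply too small and that its false-positive rate exceeds 5%. The article does not support that. It gives no correlations or SDs, and it contains hints the other way: meal-related symptom swings could make T1 the most variable rating, and T0 and T2 share an assessment setting (MRI, blood sampling, blood pressure) that T1 lacks. Either feature makes T2−T0 conservative. Adding T3 can also reverse the direction: with exponential decay on clock time, the T2−T0 type I error is 1.8% to 3.2%. This stands, and the conclusion is worded accordingly.

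It is also fair that the article names only the interaction, not T2−T0, as the target, and that the omnibus test is close to nominal. The symptom hypothesis concerns patients, whereas these figures pool patients and controls within meal arm. The Self-report section allows items to be used only where appropriate, so not every item need have all three ratings. These points limit the scope.

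Finally, a condensed article may leave residual covariance to a fuller plan, and it does not expressly exclude another structure. But it states a positive choice, the random intercept, and gives the participant effect the task of handling repeated measurements. The matched-set effect does not alter the within-subject pattern. That is a stated model open to comment, not an omitted detail.

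**Conclusion.** The point holds in limited form. As worded, the model for the symptom ratings assumes equal variance and equal correlation across T0, T1 and T2. The timing of the ratings makes this doubtful, and the nominal 5% and 95% levels are then not assured for individual allocation-by-time contrasts.

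The size is modest and its direction is not fixed by the document. For T2−T0 the type I error is about 7% to 10% if T1 and T2 are most alike with equal variances, and about 1% to 3% if T0 and T2 are most alike or T1 alone is more variable; in that second case T1−T0 runs at about 6% to 7%. Equal correlations and variances give 5%. All of this rests on assumed correlations and SDs, complete data and independent residuals around the random intercept. Only the symptom ratings are affected, not the MRI outcome or the secondary outcomes measured at T0 and T2 alone. It is worth correcting because the remedy is right whichever pattern is true.

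**What to change.** In Secondary analyses, for the visual analogue ratings, replace the subject random intercept by an unstructured within-subject covariance over the timepoints in the model, with a small-sample degrees-of-freedom method such as Kenward-Roger. Keep the matched-set random effect. Separate covariances for patients and controls are optional.

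The change is wording only. Measurement runs to the end of 2026 and analysis follows completion, so it can be fixed in advance without sight of outcome data. The cost is small. An unstructured covariance has 6 parameters for three timepoints (10 for four, if T3 is modelled), against 2 for the random intercept and residual. Error degrees of freedom for a time contrast fall from about 140 to about 70. With 72 participants the loss of precision is negligible.
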